## Abstract

**Introduction:**

Tobacco hazard is one of the most serious public health problems, accounting for up to 6 million deaths worldwide p.a. We aim to determine the efficacy and safety of acupuncture and/or nicotine replacement therapy on smoking cessation.

**Methods:**

We will recruit 96 participants who are willing to quit smoking by acupuncture and/or nicotine replacement therapy in Chengguan, Xigu and Heping Districts, Lanzhou city, for multicenter randomized, double-blind, double-dummy controlled clinical trial. Following obtained the informed consent forms, all eligible participants will be randomly divided into 4 groups: (1) acupuncture combined with nicotine patch, (2) acupuncture combined with sham nicotine patch, (3) sham acupuncture combined with nicotine patch, and (4) sham acupuncture combined with sham nicotine patch. These participants will be treated with different intervention modalities for 8 weeks and then will be followed-up for 8 weeks. The SPSS 26.0 software will be applied to analyze the clinical effects and adverse reactions of different intervention measures for smoking cessation.

**Discussion:**

This trial is a prospective, pragmatic, randomized, multicenter trial study protocol. The outcomes will illustrate the efficacy and safety of acupuncture and/or nicotine patches for smoking cessation. Provide smokers with a superior smoking cessation program.

**Trial registration:**

Chinese Clinical Trial Registry ChiCTR2100042912. Registered on January 31, 2021.

**Supplementary Information:**

The online version contains supplementary material available at 10.1186/s13063-022-06384-9.

## Introduction

Tobacco dependence is a chronic addictive disease, encoded as F17.21 in the International Classification of Diseases (ICD-10) [1]. Because cigarettes contain more than 70 carcinogens [2], long-term smokers can cause multi-organ and tissue damage, e.g., respiratory, cardiovascular, and neuromuscular diseases, and even death [3]. Quitting smoking is one of the most effective approaches to improve health condition and save lives. The benefit of reducing/quitting smoke is evidenced in improving the quality of life via decreasing the mortality and morbidity of cancer and cardiovascular diseases [4, 5]. Although there are 40% smokers who are/were willing to quit, only 8% are quitting successfully for multiple reasons [6]. Therefore, it becomes critical important to explore the effective approach to assist these remind unsuccessful quitting smokers to achieve their goal.

Nicotine replacement therapy (NRT), considered the basic treatment for smoking cessation, is the main pharmacological smoking cessation modality recommended by WHO [7]. Currently, NRT includes nicotine patches, nicotine gum, nicotine nasal sprays, and nicotine inhalers. Although nicotine patches are available for a long time within the most effective in smoking quitting [8, 9], the safety of nicotine patches is debated, partially is due to its adverse reactions, e.g., dizziness, headache, and nausea [10]. Acupuncture is a relatively common approach for smoking cessation over the past decades [11] with benefit of short-term abstinence, safety, and economic costs. During smoking cessation acupuncture significantly improves withdrawal symptoms, including upset, irritability, anxiety, and impatience experienced. However, the precise role of acupuncture for smoking cessation requires further clarification [12, 13]. Hyun S et al. demonstrate that NRT and behavioral counseling combined with auricular acupuncture are safer and more effective than traditional therapy alone [14]. However, it is still controversial about the efficacy of smoking cessation in acupuncture, NRT, and other interventions in clinical trials or related meta-analysis studies [15, 16], which remains to be validated.

It is reported that combined approach is more effective than a single intervention in improving the successful rate of smoking cessation. Therefore, this trial will use a double-blind and double-dummy randomized controlled trial, to explore the efficacy and safety of acupuncture and/or nicotine patch with placebo on smoking cessation, so as to enrich and optimize smoking cessation programs and provide effective smoking cessation methods with lower relapse rates for smokers.

## Methods

### Objectives

The objective is to explore the effect and safety of different interventional approaches, e.g., acupuncture with or without nicotine patch, nicotine patch, and placebo for smoking cessation.

### Study design

This study will be used a randomized, controlled, double-blind, double-dummy, multiple-center experimental design. We will follow the ethical principles of the Declaration of Helsinki and adhere to the principles of good clinical practice. The study is registered in the Chinese Clinical Trial Registry (registration number: ChiCTR2100042912) on January 31, 2021. The diagram is illustrated that the different phases of the study (Fig. 1 and Table 1). The Standard Protocol Items: Recommendations for Intervention Trials (SPIRIT) checklist is provided as Additional file 1 [17].

**Fig. 1 Fig1:**
[figure not shown]
The flowchart of research scheme

**Table 1 Tab1:**
[figure not shown]
The schedule of enrolment, interventions, and assessments

### Eligibility criteria of the participants

#### Diagnostic criteria

According to the Diagnostic and Statistical Manual of Mental Disorders (DSM-IV) prepared by the American Psychiatric Association, Diagnostic Criteria for Nicotine Dependence 292.0:Daily use of nicotine for at least 3 weeksMore than 4 of the symptoms that occur within 24 h after stopping or reducing smoking: dysthymia or depression, insomnia, irritability, anger, anxiety, difficulty concentrating, restlessness, slow heart rate, and increased appetite or weight gainClinically significant distress due to the above symptoms or functional deficits in social, occupational, and other important aspectsThese symptoms are not due to a physical condition and cannot be attributed to any other mental disorder

#### Inclusion criteria

Meets diagnostic criteria for smokingSmokers who voluntarily quitted smoking≥ 16 yearsInformed consent

#### Exclusion criteria

Participants with severe heart, brain, lung related system diseases and diabetesParticipants who have received other relevant smoking cessation treatment within half a monthAllergic to nicotine patch or acupuncture

#### Dropout criteria

Occurrence of serious adverse eventsThe participants withdraw spontaneouslyParticipants develop serious diseases during treatment

### Sample size calculation

We will use the calculation formula of sample size of enumeration data in a completely random design, as describe previously. The PASS software will be used for calculation. The formula is listed as follow:$$N=\frac{\Big[{Z}_{\alpha}\sqrt{2p\left(1-p\right)}+{Z}_{\beta }{\sqrt{p_1\left(1-{p}_1\right)+{p}_2\left(1-{p}_2\right)\Big]}}^2}{{\left({p}_1-{p}_2\right)}^2}$$

*α* = 0.05 will be set up as the level of test, and the test power is 90%. The withdrawal rates of acupuncture (*p*_1_) and placebo (*p*_2_) will be 56% [18] and 9.1% [19], respectively; *p* is the mean of *p*_1_ and *p*_2_. The PASS 26.0 software will be used to calculate that the sample size required for each group for ≥18 cases. Considering 30% loss to follow-up rate, the sample size per group will be 24 cases. Consequently, the total number of the participants will be 96, based on 24 case per group in the four groups.

### Randomization

A total of 96 eligible participants will be recruited from Chengguan, Xigu and Heping Districts, Lanzhou City, Gansu Province, by posters and the most popular and ubiquitous Chinese form of social media, WeChat.Sequence generation: A series of consecutive numbers (from 1 to 96) will be generated prior to the recruitment, and computer software (Microsoft Excel 2016) will be used to randomly assign each number to one of the four intervention groups (1: acupuncture combined with nicotine patch group (ACNP), 2: acupuncture combined with sham nicotine patch group (ACSNP), 3: sham acupuncture combined with nicotine patch group (SACNP), and 4: sham acupuncture combined with sham nicotine patch group (SACSNP)Allocation concealment mechanism: All will be performed in the double blind fashion. This randomization sequence will be inserted into sequentially numbered, opaque, sealed envelopes (to ensure allocation is concealed from assessors). These envelopes will be opened by the acupuncturist treating the patient

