### Recruitment

We will recruit participants from three hospitals separately, involving in the smoking cessation based on the distribution of participants. Such recruitment will be broadcasted using a few approaches, including posters and the most popular and ubiquitous Chinese form of social media, WeChat, to establish contacts with various ethnic community, university, and business groups, and conducted community-based smoking cessation programs.

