### Blinding

In this study, a randomized, controlled, double-blind, double-dummy, multi-center experimental design method will be adopted. In view of the particularity of acupuncture manipulation, it is difficult to blind the practitioners of the study. Thus, we can only blind the participants and the data collectors. The specific operation process is as follows: prior to the study, the participants will sign the informed consent, and each participant will be informed that both acupuncture and patch treatment methods would be adopted. The research group will select two groups of acupuncture points (Fig. 2, Fig. 3), so the locations of each acupuncture point may be different, but we will not inform the specific names of the acupuncture points and their effects. Because placebo patches are the exact size and shape of the patch that has already been purchased, the participants will be masked the intervention received all the time. In addition, in our data collection process, specialized data collectors send questionnaires to the research objects in the form of “Questionnaire Star,” and the data collection is completed through the network. To ensure the correct application of blindness in this study, these participants will be not aware of the grouping of the research objects.

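### The allocation envelope needlessly shows the treating acupuncturist the patch arm, and the single 1–96 list as described neither ensures 24 per group nor balances arms within the three hospitals

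*Protocol article*

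**What the plan says.** The Sample size calculation section sets a total of 96, "based on 24 case per group in the four groups". The Randomization section describes one run of numbers from 1 to 96, made before recruitment, for which Excel "will be used to randomly assign each number to one of the four intervention groups". It defines the four codes: real or sham acupuncture crossed with real or sham patch. The resulting sequence goes into sequentially numbered, opaque, sealed envelopes, and "These envelopes will be opened by the acupuncturist treating the patient". No block, quota or stratum is stated. The Recruitment section adds: "We will recruit participants from three hospitals separately".

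On masking, the Randomization section claims a double-blind procedure throughout. The Blinding section says that only participants and data collectors can be blinded, and gives the reason: "In view of the particularity of acupuncture manipulation, it is difficult to blind the practitioners of the study". It also says that the placebo patch has the same size and shape as the purchased one. The Primary outcome section has abstinence and relapse judged mainly by self-report.

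**The concern.** The two treatment factors can be masked to different degrees. An acupuncturist must know which point set to needle, but does not need to know whether the patch contains nicotine. An envelope that carries the four-way code gives away both.

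The person who receives this information sees participants more often than anyone else the article describes. What that person says or signals could affect the motivation to quit, and hence the answers that participants later give. The patch comparison would then carry an avoidable risk of bias.

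The list raises a second, lesser matter. The design counts on equal arms of 24, and three hospitals recruit separately. If the list controls neither arm totals nor the mix of arms within a hospital, differences between hospitals in practitioners or participants can become mixed with differences between arms in a trial of 96.

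**Working it through.** **1. What the envelope reveals.** Set the sections side by side:

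- Randomization: codes 1 to 4 each define needle status and patch status. Even a bare code number therefore identifies the patch arm to anyone who knows the scheme.
- Blinding: the reason for not blinding practitioners is needling. It does not extend to the patch, for which a matching sham exists.
- Acupuncture or sham acupuncture: three sessions a week in weeks 1–4 and two a week in weeks 5–8, so 3 × 4 + 2 × 4 = 20 contacts per participant.
- Primary outcome and Table 3: abstinence and relapse are mainly self-reported. Expired CO is scheduled before treatment and at week 8 only, so it offers no check at the end of follow-up.

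The patch arm is thus disclosed although the stated reason for disclosure does not cover it.

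**2. The plan's own sample size.** Inputs from the Sample size calculation section: "0.05 will be set up as the level of test, and the test power is 90" per cent, and rates that "will be 56% [18] and 9.1% [19], respectively". With p̄ = (0.56 + 0.091)/2 = 0.3255, the printed formula, taken two-sided (an assumption, as sidedness is not stated), gives

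n = [1.960 × √(2 × 0.3255 × 0.6745) + 1.282 × √(0.56 × 0.44 + 0.091 × 0.909)]² / 0.469² = 18.81.

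That is 19 rounded up, or 18 truncated, against the plan's 18. The plan's 24 follows from 18 × 1.3 = 23.4, rounded up.

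**3. Arm totals if each number is assigned independently.**

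- P(24, 24, 24, 24) = 96! / [(24!)⁴ × 4⁹⁶] = 0.00107, about 0.1%.
- The SD of one arm is √(96 × 0.25 × 0.75) = 4.24. Simulation (1,000,000 runs) gives a 95% range of 16 to 33 for one arm, a mean smallest arm of 19, and a smallest arm below 18 in 23% of trials.

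**4. Effect on power.** Two-sided, pooled-variance normal approximation for one pair of arms, averaged over 20,000 of the simulated allocations:

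| | Fixed 24 per arm | Independent assignment (mean) |
|---|---|---|
| No loss | 95.9% | 95.2% |
| 30% loss (24 × 0.7 = 16.8 per arm) | 86.1% | 85.0% |

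The average cost is about 1 percentage point.

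**5. Balance within hospitals.** The article gives no site sizes, so 32 per hospital (96/3) is assumed, with an expected count of 8 per arm per hospital. Simulation (50,000 runs):

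| | Shuffle of 24 per arm | Independent assignment |
|---|---|---|
| 95% range of a hospital-by-arm count | 4 to 12 | 4 to 13 |
| Median worst spread within a hospital | 6 | 8 |
| P(some hospital-by-arm count ≤ 4) | 35% | 61% |

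Neither way of making the list controls balance within a hospital.

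**The case against.** On the list, much of the other side's case stands.

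- A reader might infer that the list cannot yield 24 per group. The text does not say that the assignment is unrestricted. A shuffle of 24 copies of each code also fits the wording and would meet the target exactly, so the article fails to ensure 24 but does not rule it out.
- A reader might take the 23% chance of an arm below 18 as a serious loss of power. On average the loss is about 1 point. The drop below 90% after 30% loss is there with equal arms too, so it comes from the sample size and not from the randomization.
- A reader might infer that one numbered set of envelopes cannot be used in order at three hospitals. The article does not say where envelopes are held; central holding or number ranges for each hospital are possible.
- Chance imbalance by hospital under valid randomization is not bias. The 35% and 61% also depend on the assumed 32 per hospital and on the chosen threshold of 4.

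On the envelope, the Blinding section openly limits blinding to participants and data collectors, and the Discussion lists unblinded physicians as a limitation. Participant masking, which is what the double dummy chiefly serves, is not broken by the envelope. Online questionnaires also limit direct influence on recorded answers. None of this explains why the patch arm must be disclosed, and online collection does not prevent influence during treatment sessions before the participant answers.

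**Conclusion.** The envelope point holds on any reading of how the list was made. The described procedure unblinds the patch factor to the treating acupuncturist, the stated reason covers needling only, and the means to mask the patch already exists. The size of any resulting bias cannot be computed from the article. The risk rests on up to 20 contacts per participant and mainly self-reported abstinence and relapse.

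The list point holds in a limited form. No block, quota or stratum is stated, so 24 per group is not ensured. The 0.1% figure applies only under independent assignment, and the mean power cost is about 1 point. Balance within hospitals is not secured under either reading, with the 35% (shuffle) resting on 32 per hospital.

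This should be corrected because the remedy is inexpensive. It does not invalidate the trial, and the documents do not support the claim that the randomization itself is invalid or that the double dummy fails for participants.

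**What to change.** For participants not yet randomised:

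- Put only the needle assignment (real or sham point set) in the acupuncturist's envelope.
- Supply the patch as coded packs numbered by participant, prepared by someone who neither recruits nor treats.
- Generate one list per hospital in permuted blocks of randomly varying size, and do not disclose the block sizes to the acupuncturists.
- Adjust the abstinence comparison for hospital, for example with a site-stratified chi-square test or logistic regression in place of the plain chi-square test.
- Reconcile the double-blind claim in the Randomization section with the Blinding section.

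The cost is new lists and relabelled envelopes and packs. The packs must also accommodate the patch quantities in Table 2, which vary with daily smoking, weight and week. No more participants are needed. Arm totals may differ from 24 by a few if blocks are incomplete. Because the acupuncturist knows past needle assignments, blocking leaves the next needle arm somewhat predictable, which is why block sizes should vary and stay undisclosed.

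If the list is already used up, adjust for hospital and disclose in the report that acupuncturists knew the patch arm.

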### Recruitment

We will recruit participants from three hospitals separately, involving in the smoking cessation based on the distribution of participants. Such recruitment will be broadcasted using a few approaches, including posters and the most popular and ubiquitous Chinese form of social media, WeChat, to establish contacts with various ethnic community, university, and business groups, and conducted community-based smoking cessation programs.

### Blinding

In this study, a randomized, controlled, double-blind, double-dummy, multi-center experimental design method will be adopted. In view of the particularity of acupuncture manipulation, it is difficult to blind the practitioners of the study. Thus, we can only blind the participants and the data collectors. The specific operation process is as follows: prior to the study, the participants will sign the informed consent, and each participant will be informed that both acupuncture and patch treatment methods would be adopted. The research group will select two groups of acupuncture points (Fig. 2, Fig. 3), so the locations of each acupuncture point may be different, but we will not inform the specific names of the acupuncture points and their effects. Because placebo patches are the exact size and shape of the patch that has already been purchased, the participants will be masked the intervention received all the time. In addition, in our data collection process, specialized data collectors send questionnaires to the research objects in the form of “Questionnaire Star,” and the data collection is completed through the network. To ensure the correct application of blindness in this study, these participants will be not aware of the grouping of the research objects.

**Fig. 2 Fig2:**
[figure not shown]
Acupuncture points map

**Fig. 3 Fig3:**
[figure not shown]
Sham acupuncture points map

### Assignment of interventions (for controlled trials) allocation

#### Acupuncture or sham acupuncture

Acupuncture points Baihui, Lieque, Hegu, Shenmen, and Sweet points (Fig. 2) [12]. Participants will be placed in a supine position with adequate exposure of the selected acupoints and disinfection with 75% medical alcohol. For Hegu acupoint, 0.25 × 40 mm acupuncture needles will be inserted downward and vertically, and a disposable 0.25 mm–25 mm acupuncture needle will be used to insert the needle 0.5 inch downward at a 15° angle to the skin at the other acupoints. All acupoints will be fixed after needles insertion, and the presence of soreness and swelling sensation in the acupoints will be used as the standard.

Acupoints on the auricle corresponding to shoulder, eye, knee, or elbow will be taken with sham acupuncture (Fig. 3) [20]. Except for the eye points, acupuncture needles of 0.18 mm × 13 mm will be used to prick downward at a 15° angle with the skin, and the eye points will be inserted vertically into the needles and fixed.

The needle will be kept for 20 min for each time after insertion. During the period of needle retention, group 1 and group 2 will be given needle every 10 min, and a dry cotton ball will be used to press the pinhole when the needle is released. The participants will be acupunctured three times a week from week 1 to 4, and twice a week from week 5 to 8. Thus, total acupuncture time will be 8 weeks.

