## Discussion

Smoking is not only a physical dependence, but also a psychological dependence, thus, smoking cessation requires more than a strong will [21]. This study can only be carried out when the participants have certain intentions to quit smoking. We will choose two methods of NRT and acupuncture for the combined intervention of smokers who are willing to quit. Acupuncture is a relatively common and effective method in traditional Chinese medicine, while NRT is the most commonly used of the internationally recognized interventions. This combination is rarely reported in the literature, and it is expected to achieve better outcomes. We know that smoking behavior falls under the category of “mental and behavioral disorders resulting from the use of psychoactive substances” [22]. Thus, the choice of control group will not be a single intervention, but a combination of a placebo treatment of another method, as well as a group of pure placebo group. Each group will receive two interventions designed to blind the participants and provide a psychological cue that will help improve the effect of the intervention and promote participant compliance with the regulations.

There is a paradigm shift towards patient-centered care and active involvement of participants and public in research design and active participation throughout the research process [23]. However, to ensure the implementation of blind method in the later stage of the experiment, this paradigm has not adopted in the design of this study, and the protocol designers will be all composed of trial researchers, without the participation of the public or participants.

There are several limitations in the current study. First, although we chose the double dummy to try to blind the study participants, we are unable to blind the physicians, which may lead to some bias. However, all the subjective indicators are collected through the network background, which will minimize these biases to some extent. Secondly, although we have performed the sample size calculation, the sample size is still small, and a large sample test will be needed in the future stage.

Our study will evaluate the efficacy and safety of different interventions for smoking cessation, providing some evidence for smokers to choose smoking cessation programs, as well as for future studies, and promote the development of acupuncture for smoking cessation. The results will be published within 6 months after the trial completed.

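### Mid-retention needling is stated only for the two real-acupuncture groups, so practitioner contact is unmatched in every real-versus-sham acupuncture contrast

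*Protocol article*

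**What the plan says.** In the protocol article, the section *Acupuncture or sham acupuncture* sets needle retention without distinguishing the groups: "The needle will be kept for 20 min for each time after insertion". The next sentence restricts what happens during retention to two groups: "group 1 and group 2 will be given needle every 10 min". No handling, mock handling or attendance is stated for the other two.

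The *Randomization* section defines groups 1 (ACNP) and 2 (ACSNP) as real acupuncture, and groups 3 (SACNP) and 4 (SACSNP) as sham acupuncture.

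The *Blinding* section says that "the participants will be masked the intervention received all the time". It also says that practitioners are hard to blind, so only participants and data collectors are blinded. The *Discussion* describes the double-dummy logic: "Each group will receive two interventions designed to blind the participants and provide a psychological cue". It lists the unblinded physicians as a limitation and relies on online data collection to reduce the resulting bias.

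Under *Primary outcome*, abstinence and relapse rest mainly on what participants report, while expired CO is measured with a detector. Table 3 schedules CO before treatment and at week 8 only. The secondary outcomes are three questionnaire scores.

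**The concern.** A sham arm isolates the effect of needling only if what surrounds the needling is the same in both arms. As written, a practitioner who knows the allocation returns to the participant partway through each session in the real arms, with no counterpart in the sham arms. Two things then differ along with real needling: the amount of attention received, and a procedure that the participant can see and feel and might take as a sign of active treatment.

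At stake is how a difference between real and sham acupuncture is interpreted. The outcomes most open to attention and expectation are the ones on which the trial mainly relies: self-reported abstinence, self-reported relapse and the questionnaire scales. A shift in any of these caused by contact or expectation would be counted as benefit of acupuncture. The planned tests cannot separate the two, because the extra contact coincides exactly with real acupuncture.

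**Working it through.** **Which groups get the procedure.** Needling every 10 minutes is stated for groups 1 and 2. By the *Randomization* list these are exactly the two real-acupuncture arms.

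**Whether a safeguard covers it.** The *Blinding* section gives four: two sets of points whose locations may differ, withholding the names and effects of the points, placebo patches that look like the real ones, and online questionnaires. The first two concern where the needles go, the third concerns the patch, and the fourth keeps the data collector from influencing answers. None equalises what happens in the treatment room during retention.

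**How many extra contacts.** The plan gives no figure, so it is derived from the schedule in *Acupuncture or sham acupuncture*.

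- Sessions: 3 per week × 4 weeks + 2 per week × 4 weeks = 12 + 8 = 20.
- Per session: needling every 10 minutes within 20 minutes falls at 10 and 20 minutes. The 20-minute mark is when needles come out, and someone must attend for that in every group. That leaves one extra visit, at 10 minutes.
- Total: 20 × 1 = about 20 extra contacts per participant in groups 1 and 2, and none stated in groups 3 and 4.

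**Which contrasts are touched.** Four groups give six pairwise comparisons. Four cross acupuncture type (1 v 3, 1 v 4, 2 v 3, 2 v 4) and carry the imbalance. Two compare real with sham patch within one acupuncture type (1 v 2, 3 v 4) and do not.

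**What a bias would do, as an illustration only.** The documents give no size for the bias, so a range is assumed. Take no true effect and a sham quit rate p₂ = 9.1% (the placebo figure in *Sample size calculation*, read as a quit rate). Let contact or expectation raise reported quitting by b, so p₁ = p₂ + b. For a two-sided 5% test with n per arm and p̄ = (p₁ + p₂)/2:

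- SE₀ = √[2p̄(1 − p̄)/n]
- SE₁ = √{[p₁(1 − p₁) + p₂(1 − p₂)]/n}
- P(reject) = Φ[(b − 1.96·SE₀)/SE₁] + Φ[(−b − 1.96·SE₀)/SE₁]

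| Assumed b | 24 v 24 | 48 v 48 |
|---|---|---|
| 5 points | 8% | 12% |
| 10 points | 17% | 29% |
| 15 points | 28% | 51% |
| 20 points | 42% | 71% |

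The first column is one real arm against one sham arm as randomised. The second pools the two real and the two sham arms, a comparison that the article does not specify. The nominal rate is 5%. The table shows how an assumed bias would raise false positives; it does not show that any such bias will occur.

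**The case against.** The strongest reply is that the phrase about giving needle most plausibly means manipulating the needles, and that manipulation is part of real acupuncture, like the soreness and swelling sought at the real points. An active component belongs only in the active arms. That stands as far as stimulation goes. It does not explain why attendance and attention should differ too, and those can be matched without touching the active procedure.

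Second, a reader might infer that masking is broken. The documents do not support that. Each participant experiences one type of acupuncture, is told that point locations may differ, and is not told the points' effects. Nothing says that participants learn what a mid-session visit would signify. The unequal contact, however, follows from the text whether or not anyone guesses.

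Third, a reader might take the *Discussion* as promising every group an identical psychological cue, which would make this a direct contradiction. The sentence does not say that the cue is the same. The tension is with the masking claim in *Blinding*.

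Fourth, a count of 40 contacts is tempting. It includes the 20-minute visit, which coincides with needle removal in all groups.

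Fifth, the article acknowledges unblinded physicians and collects subjective data online. That limits influence at the point of data collection, but cannot undo a difference created earlier, during treatment. Expired CO is a main outcome and less open to expectation, but it is not scheduled at the end of follow-up and is not said to verify reported abstinence.

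Finally, a full protocol might describe attendance in the sham groups. The explicit restriction to groups 1 and 2 leaves little room for this, but if such text exists, the point reduces to making the article agree with it.

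**Conclusion.** The point holds as unequal practitioner contact together with a risk to masking. Followed as written, the plan builds about 20 additional contacts with an unblinded practitioner into the real-acupuncture arms only. This assumes one mid-retention visit per session, attendance at every session, and no unstated attendance in the sham groups.

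The consequence is confined to contrasts that cross acupuncture type, and within those chiefly to self-reported abstinence and relapse and the three questionnaire scores. Week 8 CO is less exposed because it does not depend on what the participant says. The direction would most likely favour acupuncture, since extra attention and any cue fall on the real arms; the size is unknown and cannot be obtained from the documents. This is an inexpensive improvement that should be made, not a defect that invalidates the trial.

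**What to change.** Reconcile the section *Acupuncture or sham acupuncture* with the masking claim in *Blinding*:

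1. State that the acupuncturist also attends groups 3 and 4 at the same 10-minute point and uses the same spoken script in all four groups. Mock attendance is enough; the sham needles need not be stimulated, and the active procedure is unchanged.
2. Add one item to the week 8 online questionnaire asking which treatment the participant believes they received, and report the answers by group. The item describes residual unmasking; it does not prevent it. Answers at week 8 may also be coloured by whether the participant has quit, so they should be read descriptively.
3. Acknowledge in the limitations that real and sham acupuncture still differ in site (sham on the auricle only), needle size and the sensation sought, and that these limit masking whatever is done about contact.

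The cost is slightly more practitioner time per sham session from staff already present, a line in the treatment procedure and one online question. No extra staff or visits are needed.
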